### Sample size calculation

Based on data from a similar healthy cohort of overweight or obese subjects in our metabolic laboratory, with a mean (standard deviation) insulin-mediated glucose uptake value of 8.1 (2.0) mg glucose per kg per minute, a sample size of 25 completing each arm is required to detect a 20 % change in insulin-mediated glucose uptake between treatment group and placebo. The 20 % increase is based on results from a study indicating the effect of vitamin D supplementation in subjects with diabetes using a comparable insulin sensitivity measurement technique and 4 weeks’ treatment [36]. Based on a type I error of 0.05 (two-tail) and a type II error of 0.20 (power = 80 %), we would require 50 participants to complete the trial.

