### Randomization

Following successful screening and baseline assessment, subjects will be randomized by a computerized randomization program to commence treatment with either vitamin D or placebo. This randomization will be done in blocks of four by sex and time of study entry (seasons) to ensure balance between the sexes in each test group and to control for the effect of seasonal change. Randomization of participants to the intervention or placebo groups will be completed by a researcher within our department (Monash Centre for Health Research and Implementation) who is not involved in the trial data collection, analysis, or reporting. This researcher will receive packaged supplements, produced by a clinical trials pharmacy, at Alfred Hospital. Capsules of vitamin D and placebo will be provided in clear containers and they will be identical and tasteless, to ensure that both participants and investigators are blinded to the treatment. To maximize compliance, participants will be provided with a calendar sheet highlighting the study period, so they can cross out each day as they go, and return the sheet along with the empty containers at the end of the study.

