#### Statistical analysis

All analyses will be conducted according to the intention to treat principle. Baseline patient characteristics will be assessed using Student’s *t* test for continuous variables and the chi-squared test for categorical variables, to check for any imbalance between the two groups. Distributional assumptions will be checked and continuous variables will be transformed if normality is violated. Baseline and within-group differences will be assessed using paired Student’s *t* tests for both primary and secondary outcome measures. The effects of the intervention on the outcomes (between-group differences) at 16 weeks will be analyzed using changes in outcome variables and linear regression. Here, the variable of interest at 16 weeks will be the outcome variable minus baseline variable, which will be additionally adjusted for baseline values. Using linear regression, pre-specified subgroups, such as age categories, sex, and body mass index will be assessed for effect modification on anthropometric, metabolic, and cardiovascular outcomes.

A separate analysis will be conducted for the severely vitamin D deficient group, who will undergo a nonrandomized mandatory treatment with vitamin D supplementation as per protocol. A within-subject analysis on primary and secondary outcome measures using paired *t* tests will be conducted on this group.

All analyses will be performed using Stata statistical software. All tests will be two-sided and *P* values of less than 0.05 will be considered statistically significant.

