### Methodological considerations

The strengths of the current study include the gold-standard study methodology, employing both randomization and double-blinding of both participants and investigators, to limit bias; the placebo-controlled design; the use of supplementary questionnaires to control for possible confounders, such as diet, physical activity, sun exposure, and seasonality; the involvement of vitamin D deficient participants; the use of an optimal dose of 4,000 IU vitamin D per day for 16 weeks, considered sufficient to raise plasma 25(OH)D concentrations; and the use of direct measures of insulin sensitivity and secretion, such as the oral glucose tolerance test, intravenous glucose tolerance test, and gold-standard euglycemic clamp, alongside comprehensive exploration of mechanisms of vitamin D action.

Despite these strengths, there are also potential limitations. First, there might be self-selection bias, given that recruitment is achieved via voluntary participation by interested subjects. These subjects might not represent the entire target population because they might be characteristically different from the volunteers (that is, potentially more health-conscious). However, randomization should serve as an effective means of minimizing this risk. Second, because we are only recruiting adults with a body mass index above 25 kg/m^2^, but who are otherwise healthy (nondiabetic, no medication, and so on), the results of the study would not be generalizable to other populations, such as those within a healthy weight range, children, or those with diagnosed diabetes or other medical conditions and comorbidities. Third, our study will only measure surrogate markers, such as blood pressure, fasting glucose, and insulin sensitivity and insulin secretion. Although these are risk factors for diabetes and cardiovascular disease, longitudinal follow-up studies would be necessary to ascertain whether a change in these risk factors translates into decreased incidence of diabetes and cardiovascular disease.

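### Randomisation is stratified by sex and season of entry, but the stated between-group regression adjusts only for the baseline value; if those factors are prognostic, the test is conservative and some precision is lost

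*Protocol article*

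**What the plan says.** Three sections of the protocol article bear on this.

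- **Randomization:** "This randomization will be done in blocks of four by sex and time of study entry (seasons) to ensure balance between the sexes". A second stated purpose is to deal with seasonal change. The number of season levels is not given.
- **Statistical analysis:** the effect at 16 weeks is estimated by linear regression on "the outcome variable minus baseline variable, which will be additionally adjusted for baseline values". No other covariate is named for this comparison. Sex returns only as a subgroup for effect modification, and season does not appear.
- **Methodological considerations:** the questionnaires are listed as a strength because they serve "to control for possible confounders, such as diet, physical activity, sun exposure, and seasonality". No model that would do this is given.

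The design figures are under Sample size calculation: "insulin-mediated glucose uptake value of 8.1 (2.0) mg glucose per kg per minute", a sample "required to detect a 20 % change in insulin-mediated glucose uptake between treatment group and placebo", "Based on a type I error of 0.05 (two-tail) and a type II error of 0.20", and "we would require 50 participants to complete the trial".

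**The concern.** Blocking within sex and season makes the two arms more alike on those factors than simple randomisation would. If the factors predict the outcome, the true sampling variance of the treatment difference falls. A regression that omits them does not register the fall: their variance stays in the residual, and the reported standard error describes a less well-balanced trial. The confidence interval is then too wide and the test rejects a true null hypothesis less than 5% of the time.

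Season is the factor that baseline adjustment is least likely to absorb. Follow-up comes about four months after entry, so usually in another season, and the article itself says (Sun exposure questionnaire) that season influences vitamin D production. On the trial's own hypothesis, season of entry could therefore shift the change score in both arms, and one baseline value cannot capture that.

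At stake are precision and calibration in a trial of 50 people, and agreement between the design, the analysis and the article's own claim about seasonality.

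**Working it through.** **1. The protocol's own figure.** The target difference is 20% of 8.1 = 1.62 mg/kg/min, with SD 2.0 and two-sided alpha 0.05.

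- Normal approximation: n per arm = 2 × (1.96 + 0.842)² × 2.0² / 1.62² = 23.9, so 24.
- Exact t-test: power is 78.4% with 24 per arm and 80.1% with 25 per arm.

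The stated 25 per arm is reproduced. The calculation takes no credit for adjustment of any kind.

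**2. Assumptions.** The documents do not supply these, so a range is shown.

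- R² is the share of variance left after baseline adjustment that sex and season explain: 0% to 40%.
- ρ is the correlation between the baseline and 16-week values: 0, 0.5 or 0.6.
- Four seasons, hence 8 strata.
- SD 2.0 applies to the 16-week value.

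Regressing change or the 16-week value on treatment and baseline gives the same treatment coefficient and standard error, so the choice of dependent variable does not matter here.

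**3. Closed form with complete balance, ρ = 0.** The baseline-only model reports about 2.0 × √(2/25) = 0.566, whatever R² is. The true standard error is 0.566 × √(1 − R²):

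- R² = 20%: 0.566 × 0.894 = 0.506
- R² = 40%: 0.566 × 0.775 = 0.438

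**4. Simulation.** 4,000 trials per scenario, N = 50, permuted blocks of four within 2 sexes × 4 seasons, effect 1.62. The baseline-only model is compared with the same model plus sex and season main effects. Simulation error is about 0.6 points on power and 0.3 points on type I error.

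ρ = 0:

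| R² | True SE, baseline-only | Reported SE, baseline-only | Type I error, baseline-only | Power, baseline-only | Power, with sex and season | Change |
|---|---|---|---|---|---|---|
| 0% | 0.567 | 0.568 | 5.2% | 80.2% | 79.7% | -0.5 |
| 5% | 0.561 | 0.569 | 4.8% | 80.2% | 81.0% | +0.8 |
| 10% | 0.553 | 0.570 | 4.0% | 79.4% | 82.4% | +3.0 |
| 20% | 0.516 | 0.572 | 3.4% | 81.2% | 86.2% | +5.0 |
| 30% | 0.493 | 0.571 | 1.9% | 82.9% | 90.4% | +7.5 |

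At R² = 40% the gain is about 11 points. The closed form puts this near the upper end:

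- Baseline-only: (1.62 − 2.012 × 0.571) / 0.438 = 1.08, power about 86%.
- Adjusted: 1.62 / 0.438 − 2.017 = 1.68, power about 95%.

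ρ = 0.5: baseline-only power is 88.8% to 92.2% for R² from 0% to 30%, and the change from adjustment runs from -0.5 to +4.5 points.

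ρ = 0.6:

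| R² | Power, baseline-only | Power, with sex and season | Change |
|---|---|---|---|
| 0% | 93.0% | 92.6% | -0.4 |
| 5% | 93.5% | 93.9% | +0.4 |
| 10% | 94.7% | 95.2% | +0.5 |
| 15% | 94.9% | 96.6% | +1.7 |
| 25% | 95.4% | 97.7% | +2.3 |
| 40% | 97.1% | 99.7% | +2.6 |

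Type I error of the baseline-only model is about 3.2% to 3.7% at R² = 15%, 2.8% at 25% and 1.6% to 1.8% at 40%. Adding the factors brings it back to about 5%.

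**The case against.** **The loss is conditional.** It exists only if sex or season explains 16-week change after the participant's own baseline is in the model. The documents give no figure, and the baseline value may already carry much of a stable sex difference. At R² = 0% the reported standard error is right and the extra terms cost about half a point of power; at 5% the gain is under one point. This stands, and it is why the point is stated conditionally.

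**The covariate list may be fuller elsewhere.** The text does not say that no other covariate enters, this is a condensed article, and a separate analysis plan may exist. This stands in part. But the Statistical analysis section is not silent on adjustment: it gives the dependent variable, the method and one covariate, and a reader who follows it would fit treatment plus baseline. That does not match the randomisation or the claim about seasonality, which is tied to questionnaires and to no model.

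**Stronger readings.** A reader might infer that the trial is underpowered, that its estimate is biased, or that false positives are inflated. The documents support none of these. The design figure of 25 per arm reproduces without adjustment, and baseline-only power was about 79% or higher in every scenario. Imbalance left by incomplete blocks is a matter of chance, not a systematic error, and the calibration error is on the conservative side. A reader might also find larger gains with a smaller target: at 1.3 mg/kg/min and ρ = 0.6, power goes from 80% to 85%, 82% to 89% and 84% to 95% for R² of 15%, 25% and 40%. The protocol's difference is 1.62, where the gain at that correlation is at most about 3 points.

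**Conclusion.** The mismatch holds as a matter of efficiency and consistency. The stated model leaves out the factors used to stratify the randomisation, and no stated analysis delivers the claimed control of seasonality. Whether this costs anything, and how much, depends on a prognostic strength that the documents do not give.

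Over the assumed 0% to 40%, with the protocol's effect and SD and 50 completers, the consequence ranges from none to a test run at about 1.6% instead of 5%. The power forgone ranges from nothing to about 3 points at baseline correlation 0.6, or about 11 points at correlation 0. These figures also rest on four season levels. The validity of the primary comparison is not threatened. The change is worth making because the possible gain clearly exceeds the possible cost.

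**What to change.** In Statistical analysis, define the between-group model for the primary and secondary outcomes as change at 16 weeks on treatment, baseline value, sex and season of entry. Enter sex and season as main effects, not as all sex-by-season cells, and use the season levels that were used for randomisation. State how many there are; four is an assumption here.

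Then align the three sections, so that Randomization, Statistical analysis and Methodological considerations describe the same handling of sex and season.

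The cost is one sentence and no new data. With four seasons the model uses 1 + 3 = 4 more degrees of freedom, taking the residual from 50 − 3 = 47 to 43, and at most about 1 power point if neither factor is prognostic.

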### Inclusion criteria

To take part in the trial, participants must be within the age range of 18 to 60 years inclusive, nondiabetic, and generally healthy, as determined by medical screening. Eligible participants must be overweight or obese (body mass index > 25 kg/m^2^). Their weight should not exceed 159 kg, owing to facility restrictions, and it should be stable, with a change of less than 5 kg in the preceding year. They should also have no intention to lose weight or change their diet or physical activity during the trial. To be included, individuals should also have a serum concentration of 25(OH)D of <50 nmol/l. However, those with frank vitamin D deficiency (<25 nmol/l) will not be randomized, but will instead be purposely allocated to the vitamin D group as allocation to placebo for 16 weeks might not be safe for these individuals.

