### Exclusion criteria

Exclusion criteria will include smoking, high alcohol use (more than four standard drinks per week for men and more than two standard drinks per week for women), hypercalcemia, allergies, diabetes (previously diagnosed or on the basis of an oral glucose tolerance test), and the use of medication, including vitamins and other supplements. Based on medical history or physical or laboratory examination, participants will also be excluded if they have any kidney, cardiovascular, hematological, respiratory, gastrointestinal, endocrine or central nervous system diseases, as well as psychiatric disorders, active cancer within the preceding 5 years, or the presence of acute inflammation. Women who are experiencing menopause, pregnant, or lactating will also be excluded.

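### Effect modification by age is to be assessed in categories although age is recorded continuously, which costs power in an already weak exploratory interaction test

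*Protocol article*

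**What the plan says.** The Statistical analysis section of the protocol article compares the arms by linear regression on the change from baseline, adjusted for the baseline value. It then says that, in the same kind of model, "pre-specified subgroups, such as age categories, sex, and body mass index will be assessed for effect modification" on anthropometric, metabolic and cardiovascular outcomes. Only age is described as categories. BMI stands in the list without a cut point and without a statement that it is continuous. Neither the number of age groups nor their limits are given. All tests use a two-sided 0.05 level, with no separate level for interactions.

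Age comes from the Inclusion criteria: "participants must be within the age range of 18 to 60 years inclusive". BMI is calculated from measured weight and height.

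The Sample size calculation covers the main comparison only: "a sample size of 25 completing each arm is required to detect a 20 % change in insulin-mediated glucose uptake", from an "insulin-mediated glucose uptake value of 8.1 (2.0) mg glucose per kg per minute". No sample size is given for any interaction.

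**The concern.** The analysis is already a regression and age is already a number, so nothing forces age into groups. Grouping treats everyone within a group as alike and puts the whole contrast at the boundary. If the response to vitamin D changes gradually with age, the grouped test is less likely to detect it than a single treatment-by-age slope. With 25 completers per arm, each half of a median split holds about 12 or 13 people per arm, so the estimate also depends on where the cut falls.

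At stake is the question this part of the plan asks, namely whether the effect differs by age. The between-arm comparison of insulin sensitivity does not depend on it.

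**Working it through.** **1. The plan's own sample size.** The target difference is 20% of 8.1 = 1.62 mg/kg/min, with SD 2.0, two-sided 0.05 and 80% power.
- Normal approximation: n per arm = 2 × (1.96 + 0.84)² × 2.0² / 1.62² = 23.9, so 24.
- With the t distribution: 24.9, so 25, and power at 25 per arm is 80.1%.

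The stated 25 per arm is reproduced. It concerns the main effect.

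**2. Information kept by grouping.** For a linear gradient, the share kept is the between-group variance of age divided by its total variance. The age distribution is not in the protocol and is assumed here.
- Uniform age on 18-60: total variance = 42²/12 = 147. The means of two halves cut at the median differ by 21, so the between-group variance is 0.25 × 21² = 110.25. Share kept: 110.25/147 = 75%; loss 25%.
- Truncated normal (mean 32, SD 10, limited to 18-60): loss 33%.
- Normal: share kept 64%; loss 36%.
- Off-centre cuts lose more: 39% for uniform age cut at 30, and 42% for the truncated normal cut at 40.
- With three equal groups the loss is 11-21%, and with four 6-14%. These apply only if a trend is fitted across the ordered groups.

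**3. Interaction power by formula, with the documented SD of 2.0.** Assume the effect rises linearly from 0 at age 18 to 3.24 mg/kg/min at age 60. The mean effect is then 1.62, and the two halves also differ by 1.62.
- Median split: SE = 2.0 × √(4/12.5) = 1.13; 1.62/1.13 = 1.43; power 29% (noncentral t, 46 df).
- Continuous age: slope per SD of age = 3.24/√12 = 0.935; SE = 2.0 × √(4/50) = 0.566; 0.935/0.566 = 1.65; power 37%.
- Difference between halves detectable with 80% power: (1.96 + 0.84) × 1.13 = 3.17 mg/kg/min, about twice the design effect.

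**4. Interaction power by simulation.** n = 50, uniform age, linear gradient, and unordered groups tested jointly. The residual SD of 1.43 is an assumption: 2.0 × √(1 − 0.7²), for a correlation of 0.7 between the two clamps.

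| Effect at age 60 (0 at 18) | SD | Continuous | 2 groups | 3 groups | 4 groups |
|---|---|---|---|---|---|
| 3.24 | 1.43 | 59% | 46% | 41% | 37% |
| 3.24 | 2.0 | 37% | 28% | 24% | 20% |
| 1.62 | 1.43 | 20% | 17% | 14% | 12% |
| 1.62 | 2.0 | 13% | 11% | – | – |

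Repeat runs differ by a point or two. More groups do not help, because the joint test spends 2 or 3 degrees of freedom. A trend score over tertiles recovers part of the loss (about 53% in the first row), but the protocol mentions none.

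**5. If the gradient is not linear.** With an effect that steps from 0 to 3.24 at age 39 (SD 1.43), continuous age and the median split have about the same power, 87% and 88%.

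**The case against.** The strongest reply is that this is one condensed sentence in a journal article. Cut points, functional form and joint or separate fitting of interactions usually belong to the analysis plan, which is not shown. That is right as far as it goes: the absence of cut points is no finding, and the protocol does call the subgroups pre-specified. But the use of age categories is a stated method, not an omission. An analysis plan that followed it would supply the cuts rather than remove them.

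A second reply is that age groups are a conventional presentation and need no linearity assumption. This also stands in part. It is a reason to show groups, less so to test with them, since even a step in mid-range costs the continuous term almost nothing.

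Several stronger readings are tempting but not supported:
- **BMI is also cut.** A reader might infer this from the word subgroups. The text attaches categories to age only, and a continuous BMI term in a linear regression fits the wording equally well.
- **The plan discards a quarter to a third of its information.** That range needs a two-group split near the median, which is not stated, and it concerns one interaction test only.
- **Continuous age would give about 60% power.** This needs an effect of 3.24 mg/kg/min at age 60, twice the design effect of 1.62, and the assumed SD of 1.43.
- **Age and sex are confounded in the oldest group.** The Exclusion criteria state "Women who are experiencing menopause, pregnant, or lactating will also be excluded", so older participants may be mostly men. The protocol has no figures to size this, and continuous age would not remove it.
- **Results will be reported from a convenient cut.** Nothing in the text suggests a cut chosen after seeing the data.

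**Conclusion.** The point holds as a minor one. The protocol plans to assess effect modification by age in categories, where a continuous term is available and, under a roughly linear gradient, more powerful at every number of unordered groups examined. For a two-group split near the median the loss is about 25-36% of the information for that interaction. In power terms this is about 13 points under the steep gradient with SD 1.43, about 9 points with SD 2.0, and about 2-3 points with half the slope. These figures rest on an assumed age distribution, linearity, 50 completers and an assumed number of groups. The form of BMI is open, so for BMI the point is only a request for clarity. The analysis is exploratory and stays underpowered whichever form is used, and no conclusion on the primary outcome depends on it.

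**What to change.** In the Statistical analysis section, replace the assessment by age categories with a treatment-by-continuous-age term, and state that BMI also enters as a continuous interaction. Check linearity, for example with a residual plot or a quadratic term. Keep age and BMI groups for display only, and describe the interaction analyses as exploratory.

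The cost is one sentence of analysis wording and no new data. The downside is that a linear trend is assumed, so a strongly non-linear pattern, such as a peak in mid-range, could be missed unless the check is done.

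If an existing analysis plan already specifies continuous terms, aligning the protocol wording with it is enough.

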## Discussion

To the best of our knowledge, this is the first clinical trial supplementing a sufficient dose of vitamin D in vitamin D deficient individuals, employing gold-standard measures of insulin sensitivity and secretion, and comprehensively investigating mechanisms of action including chronic low-grade inflammation in human beings.

Insulin resistance is common in obesity and is a key pathogenic process underpinning type 2 diabetes. Interventions that reduce insulin resistance, including lifestyle, weight loss, and pharmacological therapies, prevent and treat type 2 diabetes [53]; however, to date they have failed to slow the increasing burden of insulin resistance and resultant type 2 diabetes. Type 2 diabetes currently affects approximately 1 million Australians and, if it continues to rise at the current rate, it is estimated that this number will increase to 3 million by 2025 [31]. Diabetes is a major cause of morbidity and mortality, primarily due to an increased risk of cardiovascular disease. Moreover, Australians with type 2 diabetes require healthcare, carers, and government subsidies totalling up to 6 billion dollars in healthcare costs annually. It is vital that additional effective primary prevention strategies are established to reduce insulin resistance and prevent and manage type 2 diabetes [31]. This trial will thus inform and advance this important field.

If vitamin D supplementation improves insulin sensitivity or secretion in this trial, then with large-scale interventions, treating vitamin D deficiency could become a mainstream strategy for diabetes prevention in overweight and obese individuals who are deficient in vitamin D. Vitamin D supplementation would offer a cost-effective and easily administered intervention that could have a considerable impact on health outcomes in Australia and worldwide. In addition, vitamin D could also play a role in counteracting adverse cardiovascular events, as well as improving underlying inflammatory responses, thereby decreasing risk factors associated with a range of metabolic conditions. High-quality clinical trials, such as this, are therefore an important first step towards elucidating the true potential of vitamin D supplementation in promoting health and well-being, and reducing insulin resistance and potentially the risk of type 2 diabetes and its associated comorbidities.

Recent meta-analyses of studies examining the effect of vitamin D on type 2 diabetes and cardiovascular disease risk factors have produced largely negative results [23, 26]. Yet, some studies have suggested that improvements are only observed in vitamin D deficient individuals and only with adequate vitamin D supplementation [24, 36, 54]. Nevertheless, few trials have involved vitamin D deficient participants or provided adequate dosages, highlighting the need for trials that address these knowledge gaps.

Mechanisms of action of vitamin D might include direct and indirect effects on both insulin sensitivity and secretion, which have been investigated largely in animal and *in-vitro* studies. Vitamin D was shown to increase transcriptional activation and expression of the insulin receptor gene, which facilitates both basal- and insulin-stimulated glucose oxidation and results in improved insulin sensitivity [55–57]. Vitamin D also enhances insulin action and signal transduction by regulating extracellular calcium [58]. Vitamin D influences β-cell insulin secretion by elevating intracellular calcium, which is a crucial mechanism involved in β-cell glycolysis and the signaling of circulating glucose [29]. Vitamin D has also been implicated in the modulation of cytokine mediated β-cell apoptosis, the most important factor in the development and progression of type 2 diabetes [59, 60]. Notably, vitamin D also counteracts the harmful effects of advanced glycation products, which are essential for the development of type 2 diabetes complications and have recently been associated with the development of insulin resistance [61]. The presence of vitamin D receptors and vitamin D binding protein in pancreatic islets and nearly all inflammatory cells supports the idea that vitamin D plays a crucial role in the function of these cells, and potentially in the subsequent development of type 2 diabetes [62]. However, high-quality randomized trials remain scarce, and thus the current clinical trial plans to address this gap by comprehensively investigating mechanisms of vitamin D action *in-vivo* in human beings.

The mechanism by which vitamin D is believed to improve cardiac function and reduce the risk of hypertension is primarily via downregulating the renin-angiotensin-aldosterone system [63–66]. Vitamin D reduces levels of angiotensin II in the plasma, thereby reducing angiotensin-II-induced vasoconstriction [63–65]. Consistent with this notion, those who are deficient in vitamin D were found to have heightened levels of circulating angiotensin II, thereby increasing their risk of hypertension [63]. Vitamin D also enhances endothelial vasodilatation and modulates the flux of calcium, leading to reduced secretion of renin by juxtaglomerular cells present in vascular smooth muscle tissue, which could explain some of the antihypertensive effects of vitamin D [63–65]. Vitamin D, through its effects on advanced glycation products and oxidative stress [67], might also alleviate hypertension and reduce the risk of cardiovascular disease [68]. Another link between vitamin D and cardiovascular health is through its direct and indirect effects on lipid profiles. The indirect mechanism again refers to the calcium-regulating function of vitamin D, whereby increased calcium levels are proposed to reduce hepatic triglyceride formation and secretion [20]. It has also been suggested that vitamin D receptors improve lipid metabolism by reducing acetylated low-density lipoprotein cholesterol uptake [69]. More direct effects include the promotion of high-density lipoprotein cholesterol particle formation and the regulation of serum apolipoprotein A-1 levels by vitamin D, both of which contribute to increased cholesterol transport and overall improved lipid profiles [69–71].

Research investigating the role of vitamin D in reducing underlying chronic inflammation has also been fairly limited. However, preliminary findings suggest multiple nongenomic actions for vitamin D, alongside observed alterations in gene and protein expression following vitamin D treatment [59, 72]. For example, *in-vitro* investigations have identified the presence of vitamin D receptors in dendritic cells, monocytes and activated lymphocytes, among other inflammatory cells [62]. Moreover, 1,25(OH)D_3_ applied to isolated monocytes has been shown to regulate chemokine and cytokine secretion in patients with type 2 diabetes [72]. This in turn inhibits the pro-inflammatory actions of monocytes and decreases the proliferation and stimulatory abilities of T-cells, both of which are mechanisms thought to be due to a reduction in the expression of surface markers including major histocompatibility complex-II [72]. Where the absence of vitamin D receptors was observed, there appeared to be an escalation of pro-inflammatory activity by such cytokines as TNF-α, IL6, and CRP, which is thought to result primarily from an increase in NFκB activity [73, 29]. Supporting this notion, studies have also found that NFκB translocation appeared to be arrested, and its activity diminished, by the active form of vitamin D [74–76]. From these limited *in-vitro* studies stems the current belief that vitamin D is, at least in part, involved in regulating the signaling and stimulation of NFκB, while also controlling both separate and subsequent cytokine activity. Nevertheless, research in human beings, particularly in clinical trials of vitamin D supplementation or investigating chronic inflammation, are lacking. This trial can therefore corroborate previous knowledge, while also providing important explanations regarding the role of vitamin D in human inflammatory responses, and subsequent development of disease.

